## Abstract

**Background:**

Chronic Urticaria (CU), a common skin disorder known as Yin Zhen in Chinese medicine, is characterized by recurrent, pruritic, pink-to-red edematous lesions and wheals on the skin. Xiao-Feng Powder (XFP, meaning Wind-Dispersing Powder), is reported to be one of the most frequently used Chinese herbal formulae for CU. In this study, we aim to investigate the effectiveness and safety of modified Xiao-Feng Powder (mXFP) for the treatment of CU.

**Methods:**

In this randomised double-blind placebo-controlled clinical trial, 58 subjects identified as having mild to severe urticaria (Urticaria activity score greater than 10) will be recruited and randomised into two groups to receive antihistamine Bilastine with either mXFP or placebo for 12 weeks, followed by post treatment visits at week 16. The primary outcome measure is the change of weekly urticaria activity score (UAS7) at week 12. Secondary outcome measures include the Urticaria Control Test (UCT), Visual Analog Scale of Itch Severity (VAS), Chronic Urticaria Quality of Life Questionnaire (CU-Q2oL), Angioedema Activity Score (AAS), immunoglobulin E (IgE) test, gut microbiota test and use of antihistamines during study period. The trial will be conducted at three Chinese medicine clinics in Hong Kong.

**Expected outcomes:**

The results of this study will establish robust clinical evidence about the efficacy and safety of mXFP in the treatment of CU. A specific feature of this trial is that it is a integrative medicine trial with subjects being allowed to take the Western and Chinese medicine together for the treatment.

*Trial registration* This is registered on ClinicalTrials.gov, ID: NCT04967092. Register date: July 19, 2021. https://clinicaltrials.gov/ct2/show/NCT04967092.

## Background

Urticaria is a common skin disorder and 15–25% of people experience at least one attack of urticaria during their lifetime [1, 2]. It is characterized by recurrent, pruritic (itchy), pink-to-red edematous (swollen) lesions which usually have pale centres (wheals) [3]. The size of the lesions can range from a few millimetres to several centimetres in diameter [4, 5]. Approximately 40% of patients with urticaria also have angioedema (swelling that occurs beneath the skin) [5].

Urticaria can be divided into acute urticaria (AU) and chronic urticaria (CU) according to the disease duration. For CU, it is more common in adults, and affects women more frequently than men [5–7]. The prevalence of CU is estimated to be anywhere from 0.5 to 5% in the general population [8]. Moreover, CU can be classified as either chronic autoimmune urticaria or chronic idiopathic urticaria. In chronic autoimmune urticaria, circulating immunoglobulin G (IgG) autoantibodies react to the alpha subunit of the high-affinity IgE receptor on the dermal mast cells and basophils, leading to chronic stimulation of these cells and the release of histamine and other inflammatory mediators, thereby causing urticaria and angioedema [9]. Patients with chronic idiopathic urticaria do not have evidence of autoimmunity. In this form of urticaria, there appears to be persistent activation of mast cells, but the mechanism of mast cell triggering is unknown.

In Chinese medicine (CM), CU is known as Yin Zhen [10, 11]. Urticaria is usually associated with either internal or external wind pathogen. Wind as a pathogenic factor is characterised by sudden onset and rapid changes in symptoms, and when resulting from an internal deficiency, it often leads to dryness. A constitutional weakness, inherited from conception and/or during pregnancy, may predispose a person to CU. CU can also be caused by deficiency of Qi and blood or failure of defensive Qi in protecting the exterior. When deficiency of defensive Qi is prolonged, the patient will become more susceptible to repeated external wind attacks (CU). Persistent wind pathogen attack causes the skin dryness, leading to the development of wheals and pruritus [11–13].

In 2012, the China State Administration of Chinese Medicine issued the “Guidelines for Diagnosis and Treatment of Common Diseases of Dermatology in Traditional Chinese Medicine” [14]. Syndrome differentiation is an important feature of diagnosis in CM practice and the main syndrome types of Yin Zhen include the “Syndrome of wind-heat attacking the exterior (exterior heat syndrome)”, the “Syndrome of blockage of the exterior by wind and cold (exterior cold syndrome)”, and the “Syndrome of blood deficiency and wind-dryness” [13–15]. In addition to syndromes described above, four additional syndrome types were also described in this guideline. These include the “Damp-heat in the stomach and intestine”, the “Defence-exterior insecurity” (defensive Qi deficiency), the “Deficiency of Qi and blood”, and the “Qi and blood stagnation and stasis” [14]. The treatment strategies of CU usually aim for correcting respective aetiopathogenesis, therefore include such methods as “clearing heat and dispelling wind”, “dispelling wind and stopping itchiness”, “tonifying Qi and securing the exterior”, and “tonifying yin and moistening dryness”.

Nowadays, CM is widely used for managing CU in mainland China and Hong Kong [16, 17]. Several research groups have conducted clinical studies to evaluate the efficacy of Chinese herbal medicine for the treatment of CU in recent decades [18]. Among different Chinese herbal formulae for urticaria, Xiao-Feng Powder (XFP), literally meaning Wind-Dispersing Powder, is one of the most frequently prescribed Chinese herbal formulae for CU [19, 20].

XFP is a famous Chinese herbal formula that first appeared in the “Orthodox Lineage of External Medicine” written in 1617. It consists of *Angelicae Sinensis Radix* (Dang-Gui), *Rehmanniae Radix* (Sheng-Di-Huang), *Saposhnikoviae Radix* (Fang-Feng), *Cicadae Periostracum* (Chan-Tui), *Anemarrhenae Rhizoma* (Zhi-Mu), *Sophorae Flavescentis Radix* (Ku-Shen), *Sesami Nigrum Semen* (Hu-Ma), *Schizonepetae Herba* (Jing-Jie), *Atractylodis Rhizoma* (Cang-Zhu), *Arctii Fructus* (Niu-Bang-Zi), *Gypsum Fibrosum* (Shi-Gao), *Glycyrrhizae Radix et Rhizoma* (Gan-Cao) and *Akebiae Caulis* (Mu-Tong). XFP has been widely used in Chinese medicine dermatology to expel wind and eliminate dampness, clear heat, nourish the blood and stop itchiness [21]. Moreover, other researchers have found that XFP is effective in inhibiting inflammation, allergy, and oxidative stress in allergic skin diseases [22]. This formula is applicable for urticaria due to wind, dampness, and heat invading the body and settling in the blood vessels where it is unable to vent externally or drain internally. The symptoms that can be managed by XFP include itchy skin, red rashes and weeping upon scratching. This formula serves as the common formula for urticaria and eczema caused by wind-heat or wind-dampness trapped between the skin, striae, and interstices.

This clinical study aims to determine the effectiveness and safety of modified Xiao-Feng Powder (mXFP) for the treatment of CU. A randomised, double-blind, placebo-controlled clinical trial design with strong scientific rigor will be employed in this study. In the study, we will use comprehensive outcome measures to evaluate the treatment response. Furthermore, we will perform gut microbiome analysis to explore the relationship between the treatment effect of mXFP and the modulation of gut microbes. By collecting subject’s fecal samples, the richness of 16S rDNA and the biodiversity in each gut microbiome sample can be compared before and after taking mXFP [23]. This clinical study will be able to provide robust clinical evidence on the efficacy and safety of mXFP for CU.

### Objectives

The objective of the study is to evaluate the clinical efficacy and safety of mXFP on patients with CU.

## Methods

### Study design

It is a multi-centred, randomized double-blinded placebo-controlled clinical trial with treatment duration of 12 weeks and post-treatment follow-up period of 4 weeks. We will randomly allocate the eligible subjects into two groups to receive either mXFP or placebo twice daily for 12 weeks followed by post treatment visits at week 16. Subjects will also take antihistamine standard therapy regularly for the first 6 weeks, and then for on-demand basis for the next 6 weeks during the treatment period.

### Inclusion criteria

Men and women aged from 18 to 65 years with mild to serve chronic urticaria, who can provide informed consent for the participation, complete questionnaires and take medications as scheduled, are included. Chronic urticaria with mild to serve activity is defined by the following criteria:Documented history of CU for at least 6 weeks prior to entry in the study;Meet EAACI/GA^2^LEN/EDF/WAO 2017 guidelines, i.e. spontaneous appearance of wheals, angioedema or both for > 6 weeks due to known or unknown causes; andSymptom severity must be greater than 10 points (UAS7 score).

### Exclusion criteria

Subjects are excluded if they meet the any one of the following criteria:Dual deficiency of Qi and blood according to Chinese medicine theoryUrticaria is induced by physical factors (e.g., cold urticaria, delayed pressure urticaria, solar urticaria, heat urticaria, vibratory angioedema) only;Known to have dermatological diseases with skin pruritus;Known to have any serious diseases such as cancer, severe kidney and liver impairments, autoimmune disease, thyroid disease, Hodgkin’s disease, lymphoma, severe mental disorders, leukemia, and acute infectious disease;Known to use oral/injectable corticosteroids, leukotriene inhibitors, immunosuppressants or other Chinese herbal medicine within one month of enrollment;Known to receive omalizumab, ligelizumab, or other experimental biologic for CU;Documented pregnancy or planning to conceive, breast-feeding women; orOperate heavy machinery or need to drive motor vehicles as an essential part of their profession.Known to recent history (within previous 12 months) of drug addiction or alcohol abuse.Involved in other interventional clinical studies at the same time.Use antibiotics, prebiotics and probiotics within 4 weeks before study treatment commencement.

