### Intervention

In this trial, the dose of standard therapy of antihistamine, Bilastine, is 20 mg once daily during the first 6 weeks of treatment, and on-demand basis during 6th-12th weeks. Participants will be allowed to increase dose of Bilastine up to 20 mg stat dose in case of insufficient control of symptoms according to EAACI/GA2LEN/EDF/WAO 2017 guidelines [3]. The dose of the investigational Chinese medicine formula granules, mXFP, is 19.4 g each time, twice daily in the treatment group while the placebo granules is 19.4 g each time, twice daily in the control group. All participants will be randomly assigned at a 1:1 ratio into two groups to receive the granules.

Moisturiser is not prohibited for use during the study. However, any additional treatment other than the standard western therapy and Chinese medicine granules after randomization is prohibited. Besides, participants will not be allowed to take prebiotics and probiotics during the study.

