### Randomisation and blinding

A random number table will be generated with a computerized random number generator program. The random allocations will be put into opaque envelops with sequential study numbers. Two sets of the envelope will be prepared, with one set for randomization at the site and another set stored in the investigator’s office for emergency unblinding. Each participant will be assigned with a sequential study number and then the corresponding allocated herbal granules or placebo will be prepared according to the random allocation sequence by an independent research staff member. The dosages will be prepared according to CMP’s instruction. During the study, the CMP investigators, study participants and outcome assessors will be kept blind of the allocated intervention.

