### Trial procedures and follow-up

As shown in the Fig. 1 and Table 1, each partcipant has a phone call or face-to-face interview in screening and a total four visits to the Chinese medicine clinic throughout the study. Community participants who express interest in our study and agree for our telephone screening will leave their contact to project research assistant while potential participants referred from the wards, clinics or medical centres will be screened directly. Eligible subjects after screening will be arranged for a face-to-face or telephone interview for eligibility assessment. UAS7 will be delivered and filled by participants 7 days before the baseline visit.

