**Fig. 1 Fig1:**
[figure not shown]
Study flow chart

**Table 1 Tab1:** SPIRIT schedule of enrolment, interventions, and assessments

	Study period				
	Screening	Treatment period			Post treatment follow up
Timepoint	−7 to 0 days	Day 0 (baseline)	Week 6 (±4 days)	Week 12 (±4 days)	Week 16 (±4 days)
Enrolment					
Informed consent	X				
Eligibility screen	X	X			
Medical consultation and assessment	X	X	X	X	X
Medical history	X				
Concomitant medication	X	X	X	X	X
Intervention					
mXFP/ Placebo and Bilastine		X	X		
Outcome Assessment					
Weekly urticaria activity score (UAS7)	X	X	X	X	X
Urticaria Control Test (UCT)		X	X	X	X
Visual Analog Scale of Itch Severity (VAS)		X	X	X	X
Chronic Urticaria Quality of Life Questionnaire (CU-Q2oL)		X	X	X	X
Angioedema Activity Score (AAS)		X	X	X	X
Serum levels of IgE	X			X	
Gut microbiota		X		X	
AE/SAE assessment			X	X	X
Laboratory Assessment					
CBP with differentiation	X			X	
Renal and Liver function test	X			X	
Thyroid function test (FT3, FT4 and TSH)	X				

For the baseline visit, eligibility will be checked and information about the study will be explained to the participants who will sign informed consent form voluntarily at their agreement afterward. Participants will be taken for not more than 20 ml of blood for complete blood count (CBC), liver function test (LFT), renal function test (RFT), and thyroid function test (FT3, FT4 and TSH) as safety measures while total immunoglobin E (IgE) as one of the outcomes for the measurement of inflammation. Then participants will be randomly assigned at a 1:1 ratio to receive 6 weeks of either mXFP granules 19.4 g each time or placebo granules 19.4 g each time twice daily. All participants will take the standard therapy of Bilastine 20 mg once daily during the first 6 weeks of treatment, and on-demand basis for the subsequent 6 weeks. They will be allowed to increase the dose of oral Bilastine up to 20 mg stat dose in case of insufficient control of symptoms according to EAACI/GA2LEN/EDF/WAO 2017 guidelines [3]. Baseline demographic data, medical history and drugs including use of moisturiser will be taken. UAS7, UCT, VAS, CU-Q2oL, and AAS will be completed. Participants will start study treatment after stool collection and notification of non-clinically significant blood results for the safety measures. Relevant information on the use and storage of study drugs will be recorded.

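### The UAS7 that sets eligibility and baseline carries no antihistamine condition, so equal baseline scores can mean treated or untreated disease; adjusting for diary-week antihistamine use would recover precision at almost no cost

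*Protocol article*

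**What the plan says.** **Prior medication.** The Exclusion criteria set a one-month limit for some classes: "Known to use oral/injectable corticosteroids, leukotriene inhibitors, immunosuppressants or other Chinese herbal medicine within one month of enrollment". They set four weeks for antibiotics, prebiotics and probiotics, and also exclude patients who receive biologics. Antihistamines, the class given to both arms, appear nowhere in the list.

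**Entry score.** The Inclusion criteria require a UAS7 above 10. They do not say whether it is scored on or off an antihistamine.

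**Timing.** Under Trial procedures and follow-up, "UAS7 will be delivered and filled by participants 7 days before the baseline visit". Table 1 gives a screening window of 7 days up to Day 0 and shows no other pre-treatment period. The Intervention section restricts other treatment only from allocation onwards: "any additional treatment other than the standard western therapy and Chinese medicine granules after randomization is prohibited".

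**Background treatment.** After the baseline visit, "All participants will take the standard therapy of Bilastine 20 mg once daily during the first 6 weeks of treatment", then on demand for the next 6 weeks. Table 1 places this at Day 0, although the text below it adds: "Participants will start study treatment after stool collection and notification of non-clinically significant blood results for the safety measures".

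**Records, allocation and analysis.** Prior drugs are recorded ("Baseline demographic data, medical history and drugs including use of moisturiser will be taken"), and Table 1 lists concomitant medication at both screening and baseline. The allocation list is described only as "A random number table will be generated with a computerized random number generator program", with no stratification factor named. The primary analysis is an ANCOVA of UAS7. Adjustment for further baseline covariates is mentioned only for the secondary outcomes, without naming them.

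**The concern.** The trial asks what mXFP adds to bilastine, and the primary outcome is the change in UAS7 at week 12. Consider two patients who both score 15 in the diary week. One has taken no antihistamine and is about to start one. The other scores 15 despite taking one regularly and will move to bilastine. Whatever mXFP does, the first has a bilastine response still to come, while the second may have little more to gain from that class. Their expected week-12 scores may differ, yet they enter an ANCOVA on baseline UAS7 with the same covariate value.

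Any such difference stays in the residual. With 58 patients and no balancing on this factor, it can also fall unevenly between the arms by chance. What is at stake is the precision of the primary estimate. The information needed to recover some of it is apparently already collected.

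**Working it through.** **1. The plan's own figure.** Inputs from the Sample size section: difference 10, SD 12, power 80%, significance level 0.05 (two-sided, from the Statistical analysis plan section).
- Normal approximation: n = 2 × (1.960 + 0.842)² × 12² / 10² = 22.6, so 23 per group.
- Noncentral t: 24 per group, with power 80.7%.
- Total: 1 − 48/58 = 17.2% implied dropout.

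The stated 24 per group and total of 58 stand and are not in dispute.

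**2. What baseline UAS7 can and cannot carry.** Entry and baseline rest on a score from the week before treatment. No rule fixes antihistamine use in that week. From the start of treatment, everyone is on the same bilastine schedule. The change in antihistamine exposure between baseline and follow-up therefore differs by patient, and the score itself does not reveal it.

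**3. Precision recovered by adjusting.** Let R² be the share of residual variance (after treatment and baseline UAS7) explained by diary-week antihistamine use. The documents do not give it, so a range is assumed. SD 12 is taken as the total residual SD.
- Adjusted SD = 12 × √(1 − R²)
- Equivalent sample gain = 1/(1 − R²)

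| R² (assumed) | Adjusted SD | Equivalent gain |
|---|---|---|
| 10% | 11.4 | 1.11, about 11% more patients |
| 20% | 10.7 | 1.25, about 25% more patients |

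**4. What that range implies.** Suppose a share p of patients took no antihistamine in the diary week, and at equal baseline UAS7 they improve by D more points in both arms. Then R² = p(1 − p)D²/144.
- p = 0.5: R² = 10% needs D = √(14.4/0.25) = 7.6. R² = 20% needs D = √(28.8/0.25) = 10.7.
- A smaller gap gives less: with p = 0.5 and D = 5, R² = 6.25/144 = 4.3%, a gain of 1/(1 − 0.043) = 1.045, or about 4.5%.

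The 11% to 25% range therefore assumes a response gap of roughly 8 to 11 UAS7 points with an even split.

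**5. Chance imbalance.** With 24 per arm and p = 0.5, the between-arm difference in p has SD √(2 × 0.25/24) = 14.4 percentage points. A difference of 20 points or more has probability of about 17%. With 29 per arm these become 13.1 points and about 13%. If D = 10, one SD of imbalance at 24 per arm moves the contrast by 0.144 × 10 = 1.4 UAS7 points. The standard error of the difference is 12 × √(2/24) = 3.5, so the shift is about 0.4 standard errors.

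**The case against.** **No bias.** The strongest reply is that nothing here biases the comparison. "All participants will be randomly assigned at a 1:1 ratio into two groups to receive the granules", both arms receive the same bilastine schedule, and the placebo arm absorbs any bilastine response. Prior antihistamine use is a prognostic factor like many others. This stands in full. A reader who infers that the treatment effect is confounded would be wrong.

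**No loss of stated power.** A reader might also infer that the trial is underpowered. If 12 were the SD within antihistamine subgroups and D = 10 were added on top, power at 24 per arm would fall to 74–76%. The documents do not support that reading. The SD comes from an earlier study of Chinese patients with chronic urticaria, and whether it already includes mixed prior treatment cannot be seen. With 12 as the total SD, the stated power holds and adjustment is a bonus.

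**No floor argument.** It is tempting to say that patients entering just above 10 leave no room for a 10-point gain. But 10 is a difference in group means, no mean baseline is given, and bilastine is on demand in the 6 weeks before the week-12 endpoint. A covariate would not change a floor in any case.

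**No bilastine-refractory subgroup.** The documents do not describe prior bilastine use or response. They only leave prior antihistamine use open.

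**Covariates belong in the SAP.** The choice of covariates is commonly left to an analysis plan, which is not shown, so failing to list them here is no fault. What remains is narrower: the stated eligibility rules and schedule create one identifiable source of variance that baseline UAS7 cannot absorb. Broad entry may also be deliberate, since the Discussion defends a regimen close to daily practice. That supports keeping the entry criteria, and adjusting does not conflict with it.

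**The imbalance is modest.** A shift of 0.4 standard errors is ordinary sampling error that the confidence interval already covers. That is correct. Adjustment reduces this error but does not repair an invalid test.

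**Conclusion.** The point holds as one about precision. The baseline and eligibility UAS7 are taken under unspecified antihistamine conditions. Baseline adjustment alone cannot separate treated from untreated disease at the same score, so some avoidable variance and chance imbalance remain in the primary comparison. The between-group contrast is unbiased, and the sample size reproduces with no shown loss of power.

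The gain from adjusting is about 11% to 25% in equivalent sample size if the factor explains 10% to 20% of residual variance, and less if the response gap is small (about 4.5% at 5 points with an even split). The explained share, the proportion of patients on antihistamines and the response gap are all assumptions, because the documents give none of them.

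**What to change.** From the concomitant-medication record at screening and baseline, derive antihistamine use during the baseline UAS7 week: none, as needed or regular. Collapse to any versus none if cells are small, with the collapsing rule written down in advance. Add this factor, together with baseline UAS7, to the week-12 ANCOVA, and fix that choice before unblinding. Before relying on it, confirm that the record distinguishes as-needed from regular use and dates it to the diary week.

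Any table of the treatment difference by this factor should be descriptive only. With about 29 per arm, subgroup estimates would be very imprecise.

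The cost is one derived variable and one degree of freedom, or two with three categories. Treatment, visits, eligibility and sample size do not change. Whether antihistamine use before baseline should be controlled is a clinical matter for the investigators, and nothing is proposed on it here.
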